### Interventions

#### Treatment group intervention

##### Trainers and participants

The treatment group will receive social skill intervention using music therapy in groups of eight. A certified music therapist with prior experience with children with ASD and ID will be the trainer for the treatment group. Parents or primary caregivers will be invited to attend the intervention sessions and to observe the training. An assistant trainer will also be present in all sessions to facilitate the group activities, manage unexpected situations, and ensure the safety of the participants.

##### Schedule and setting

The intervention will be delivered one session per week over a 12-week period. The sessions are 45 min in duration and are designed to be short because children with ASD and ID tend to exhibit a short attention span. The location will either be at a special schools or NGO in Hong Kong.

##### Session structure

Each session will follow a similar structure with a hello song, musical activities, and a goodbye song. The musical activities will vary in each session and will be mixed in later sessions to revisit and practice social skills [6].

##### Intervention contents and target skills

Session 1–2: Familiarize the participants with the surroundings and other participants and the music therapy session structure using visual display; introduce the hello and goodbye songsSessions 3–4: Increase vocalization and verbal use by song singing of familiar songs and social songsSessions 5–6: Encourage communication of choice, sharing, and social interaction by selecting, using, and exchanging musical instrumentsSessions 7–8: Emphasize group participation and sending and receiving social cues by group drumming and music making, and other coordinated movements during songsSessions 9–10: Increase initiation, response, and turn-taking by free or structured improvisations of vocal and instrumental musicSession 11–12: Review and reinforce past musical activities, appreciate and reward improvements, forewarn the end of intervention sessions

##### Emphasis of approach

The trainer will typically focus on building a relationship with the participants, understanding their current levels of functioning, and choosing musical activities that may scaffold their social development.

#### Control group intervention

##### Trainers and participants

The control group will receive behavioral-based social skill training in groups of eight. The trainer will be a registered social worker with experience in providing social skill training for children with ASD and ID. Parents or the primary caregivers will be invited to attend the intervention sessions and to observe the training. An assistant trainer will also be present in all sessions to provide support.

##### Schedule and setting

The intervention schedule will closely follow the treatment group’s schedule, with one 45-min session per week for 12 weeks. The location will either be at a special school or NGO in Hong Kong, using the same venue if feasible.

##### Session structure

Each intervention session will follow a standard structure of opening greetings, social activities according to the theme of the session, and a closing activity. The activities and games will vary in each session and will be mixed in later session to revisit and practice social skills [14].

##### Intervention contents and target skills

Session 1–2: Familiarize the participants with the surroundings and other participants and the intervention session structure using visual display; introduce greetings and gestures when meeting new people and making friends via visual and video modelingSessions 3–4: Increase vocalization and verbal use by playing pair and group games and small craft projects that require collaboration and communicationSessions 5–6: Encourage communication of choice, sharing, and social interaction by reading social stories and playing cooperative gamesSessions 7–8: Emphasize group participation and sending and receiving social cues by role-play; exercises in recognizing emotions and display of appropriate emotions and behaviors in different daily settingsSessions 9–10: Increase initiation, response, eye contact, and turn-taking in conversation by explicit instructions or demonstrations, small group practice with feedbackSession 11–12: Review and reinforce past activities and taught social skills, appreciate and reward improvements, forewarn the end of intervention sessions.

##### Emphasis of approach

Focus is typically on explicit and concrete instructions, reinforcing good social habits, and fostering positive associations for group interactions. Musical activities will be excluded in this control condition to contrast the specific effects of music therapy in intervention. This type of group training is typically offered by schools or NGOs in Hong Kong for children with ASD with or without ID, and may be considered as a standard practice control condition relative to music therapy targeting social skills.

### Assessment of treatment fidelity

Before intervention commences, the intervention manual will be shared with the trainers to facilitate their preparation and delivery of intervention. All materials and procedures that have been developed will be clearly described and explained in pre-intervention meetings with trainers. Adherence to the protocol and trainer competence will be directly assessed by the recorded video data and by independent review of the intervention session notes. The inter-trainer reliability and evaluation of treatment integrity will be reported in the outcomes. Participants will be asked for reasons for discontinuation or deviation from intervention protocols.

### Outcome measures

#### Primary outcomes

The primary outcome measure is autistic severity as assessed using a standardized rating scale by an independent rater who will be blinded to the study group allocation. This outcome was selected because observing behavioral changes that generalize to other social contexts outside of the intervention is the ultimate goal of social skill intervention. Parental rating by using a standardized rating scale is included as another outcome to support the clinical assessment. Parents are good informants because they spend time with the participants outside of intervention contexts, but they are not blinded to the group assignment and may exhibit expectation biases. Another outcome is the behavioral changes at the last intervention sessions relative to the first session. Trained research assistants who are blinded to the session number and study hypotheses will code for target social behaviors by using video data. This measurement will provide an objective measure of the social skills exhibited by participants within the intervention setting.

##### CARS-2

The general autistic symptoms of the participants will be assessed using CARS-2 [15], by a qualified and experienced assessor. This scale consists of 15 questions rating the autistic symptoms and general impression of deviance based on behavioral observations. Each question is rated from 1 to 4, and high scores are associated with a high level of impairment. Scores below 30 indicate that an individual does not have ASD, scores between 30 and 36.5 imply mild to moderate autism, and scores from 37 to 60 correspond to severe autism. The psychometrics of CARS-2 is well documented in Western and Chinese contexts [15, 16].

##### SRS-2

Parental ratings of generalized social interaction outcomes will be collected using SRS-2. A parent of each participant will be asked to complete the SRS-2 based on their observations of their child over the previous 3 months. The scale is a 65-item questionnaire that measures the severity of social impairments associated with ASD [17]. The five subscales include social awareness, social cognition, social motivation, social communication, and autistic mannerisms. Each item is rated on a scale from “0” (never true) to “3” (almost always true), and high scores indicate severe social impairments. SRS-2 exhibits good psychometric properties in Western and Chinese contexts and is sensitive to changes in social functioning among children with ASD [17, 18].

##### In-session social behavior

The intervention sessions in the treatment and control groups will be videotaped using a high-resolution video camera, and data from the first and last sessions will be coded for target social behavior. The three main types of behavior, namely, initiation, turn taking, and eye contact, will be examined using a microanalysis of video recordings in one-second intervals [19]. Target social skills were selected based on the expected types of behavior that may occur during the sessions and that are essential for effective social interactions. The frequency and duration of the social behavior will be recorded with the following coding scheme. Initiation includes touching a person, making a verbal request, giving an object to a person, and other actions to get another’s attention. Turn taking includes responding within an appropriate time either verbally or non-verbally and not interrupting out of turn. Eye contact includes directing the gaze toward the person speaking or acting. The behavior will be further categorized as instructor-to-participant social interactions or participant-to-participant social interactions. Inter-rater reliability will be determined in 20% of coding. These behavioral outcomes are important indices of how much and how appropriately children engage in social interactions. Video data from each session will also be used to indicate the amount of explicit instruction (talking time of the trainer) and amount of music use, to validate the fidelity of the interventions. These data may be included as covariates in data analyses if they are significantly different across groups.

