**Method:**

A randomized controlled trial (RCT) with two parallel groups of 40 children each (1:1 allocation ratio) is planned. Participants will receive 45 min of music therapy or non-musical intervention targeting social skills once a week for 12 weeks. Primary outcome measures will be independent ratings on the Childhood Autism Rating Scale and parent ratings on the Social Responsiveness Scale-2. Linear mixed-effects models for these two outcome measures will be created for data collected at 2-week pre-intervention, 2-week post-intervention, and 4-month post-intervention sessions. In-session behaviors at the first and last intervention will be videotaped and coded offline and compared. Pretreatment neural response of quantitative electroencephalograms (qEEG) to social scenes will be used to predict the outcomes of musical and non-musical social skill interventions, whereas qEEG responses to music will be used to predict the effectiveness of musical social skill intervention.

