### Statistical analyses

Interim analyses will not be performed and data collection will continue until the intended sample size is reached. The investigators and research assistants will have full access to the final trial dataset. Analyses will focus on hypothesis-driven testing with separate models for each outcome measure by using linear mixed effect modeling if the assumptions for linear effects are met [21]. This regression-based statistical test can be used to evaluate multiple categorical and continuous predictors, and eliminates the need to run multiple tests for different hypotheses, which inflates the risk for type I error. Attrition bias will be assessed by comparing the participant completion rate in the two conditions and considering the reasons. Mixed effect models are robust with missing or extreme values, which is useful if the attrition rate for the 12-week intervention is higher than expected. Fixed effect predictors will be intervention type (music/non-music), time (pre−/post-intervention), and pre-treatment EEG frontal asymmetry (social and music). The random effects of participants and groups will be included to estimate random errors arising from individual differences in participants and group trainers. Control factors will include overall and verbal IQ, age, and ASD severity. The inclusion of these covariates alleviates concerns on unreliable effects due to the heterogeneity of children with ASD and ID.

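### In-session social behaviour, placed under the primary outcomes, is coded as up to 12 measures with none named as deciding, and the mixed models do not remove that multiplicity

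*Protocol article*

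**What the plan says.** **Status.** In the protocol article, In-session social behavior is the third subheading under Primary outcomes, after CARS-2 and SRS-2 and before Secondary outcomes begins. The opening text of Primary outcomes ranks the measures differently: "The primary outcome measure is autistic severity as assessed using a standardized rating scale by an independent rater". In-session behaviour then appears as a further single outcome: "Another outcome is the behavioral changes at the last intervention sessions relative to the first session". The abstract does not count it as primary: "Primary outcome measures will be independent ratings on the Childhood Autism Rating Scale and parent ratings on the Social Responsiveness Scale-2".

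**Coding.** In-session social behavior defines "The three main types of behavior, namely, initiation, turn taking, and eye contact". It adds that "The frequency and duration of the social behavior will be recorded with the following coding scheme", and then: "The behavior will be further categorized as instructor-to-participant social interactions or participant-to-participant social interactions". The article gives no summary score and no order among these measures, and calls none of them exploratory.

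**Analysis.** Statistical analyses plans "separate models for each outcome measure by using linear mixed effect modeling". It says of this regression approach that it "eliminates the need to run multiple tests for different hypotheses, which inflates the risk for type I error".

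**The concern.** An outcome announced as one thing becomes a family of measures once the coding scheme is read. If each member can be compared between arms at 0.05 with no deciding measure, a significant result on one of them is weak evidence, and a reader of the final report could not tell whether the measure was chosen before or after the data were seen. The partner types add a further difficulty: an arm difference in interactions with the instructor but not with other children, or the reverse, has no rule to settle it.

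This is more than detail left to an analysis plan, because the article takes a position on multiplicity and that position is wrong for this case. One model with several predictors can replace several separate tests of those predictors on one outcome. It does nothing about repeating the between-arm comparison on several outcomes, which is what separate models per outcome measure entail. A team following the text would believe it had a protection that it does not have.

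**Working it through.** **Stated figure.** The article gives no error rate for this outcome, so there is none to reproduce.

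**Inputs from the article.**
- Behaviours: 3. Metrics: 2 (frequency, duration). Partner types: 2. All are from In-session social behavior.
- α = 0.05, from Sample size calculation. Sidedness is not stated; two-sided is assumed here.

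**Inputs assumed.**
- The correlation ρ between test statistics is not given. A common ρ from 0 to 0.9 is used.
- The number of measures tested, k, is not given. The values 12, 6 (behaviour × metric) and 3 (behaviours only) are used.

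**Count.** 3 × 2 × 2 = 12.

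**Independent tests.** P(at least one false positive) = 1 − (1 − α)^k.
- k = 12, either direction: 1 − 0.95^12 = 0.460.
- k = 12, favouring music only: 1 − 0.975^12 = 0.262.
- k = 6, either direction: 1 − 0.95^6 = 0.265.
- k = 3, either direction: 1 − 0.95^3 = 0.143.

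**Correlated tests.** For k equicorrelated standard normal statistics with two-sided critical value c:

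P = 1 − ∫ [Φ((c − √ρ·t)/√(1−ρ)) − Φ((−c − √ρ·t)/√(1−ρ))]^k φ(t) dt.

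For the favourable direction only, the second Φ term is dropped, so each test has a false-positive rate of 0.025. Numerical integration gives:

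| ρ | k = 12, either direction | k = 12, favouring music | k = 6, either direction | k = 3, either direction |
|---|---|---|---|---|
| 0 | 46.0% | 26.2% | 26.5% | 14.3% |
| 0.3 | 39.7% | 20.2% | 24.1% | 13.6% |
| 0.5 | 31.9% | 16.0% | 20.7% | 12.5% |
| 0.7 | 23.2% | 11.6% | 16.4% | 10.9% |
| 0.9 | 13.5% | 6.7% | 10.8% | 8.4% |

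**Reference values.** One named measure gives 5% in either direction and 2.5% favouring music.

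**Inflation at ρ = 0.5, k = 12.** Either direction: 31.9 / 5 = 6.4 times nominal. Favouring music: 16.0 / 2.5 = 6.4 times nominal.

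**The case against.** The strongest reply has four parts.

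1. **The text describes coding, not hypotheses.** Behaviours are recorded and categorised; the article nowhere says that 12 between-arm tests will be run. Partner type could be a factor within one model. This stands: 12 is an upper count, and the results have to be shown for smaller k as well. Even three tests exceed 5% at every correlation considered.

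2. **The link to the separate models is not secure.** The abstract attaches the linear mixed-effects models to CARS and SRS-2 and says only that in-session behaviours are coded and compared. The time factor in Statistical analyses is pre- versus post-intervention, not first versus last session. This stands in part. Statistical analyses speaks of each outcome measure without excepting the in-session one, so the article leaves the matter open. Comparing the measures by another method would bring the same multiplicity.

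3. **The outcome is not the one on which the trial is judged.** A reader might infer from the heading that the main conclusion hangs on the in-session result. The documents do not support that: the text names blinded-rated autistic severity as the primary measure, the abstract lists only the two rating scales, and the video measure is described as reflecting skills within the intervention setting. This stands and limits the weight of the point. The placement under Primary outcomes still needs to be reconciled.

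4. **Ranking the components of a supporting outcome is commonly left to an analysis plan.** That is fair for the missing summary score or order alone. It does not cover the sentence on type I error, which is in the article and is incorrect across outcomes.

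**Conclusion.** The point holds in limited form. In-session behaviour has an inconsistent status, up to 12 measures and no deciding one, and the article's statement on type I error does not apply to multiplicity across outcomes.

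If all 12 measures are tested at two-sided 0.05, the chance of at least one false between-arm difference is about 13.5% to 46% in either direction, and about 7% to 26% favouring music against a nominal 2.5%. If only the three behaviours are tested, it is about 8% to 14% in either direction. These ranges rest on a common correlation between 0.9 and 0, which the article does not give.

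A reader might infer a false improvement rate of about 32%. The documents do not support that. The 32% counts significant differences in either direction, and it needs all 12 tests and an assumed correlation of 0.5. At that correlation the rate favouring music is 16%; with two-sided tests and non-negative common correlation it does not exceed 26%.

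The CARS-2 and SRS-2 comparisons are not affected by this point. What is at risk is any claim of benefit drawn from the video data.

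**What to change.** 1. In In-session social behavior, name one measure (behaviour, metric and partner type) for the between-arm test. Alternatively, test the three behaviours on one stated metric, with the handling of partner type also stated, using Holm adjustment.
2. Label the remaining measures exploratory and report them with estimates and intervals, without significance claims.
3. In Primary outcomes, state that the in-session outcome supports the rating-scale outcomes, so that heading, text and abstract agree.
4. In Statistical analyses, correct the multiplicity sentence: a mixed model can combine several predictors of one outcome, but separate models for several outcomes still need a deciding measure or an adjustment.

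The cost is wording only. The video coding is unchanged and every measure can still be reported. The small downside is that the remaining measures can no longer support a confirmatory claim.

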#### Secondary outcomes

EEG will be recorded using Epoc X (EMOTIV) research-grade EEG headsets with 14 channels digitized at 256 Hz. This tool is a child-friendly wireless mobile EEG system that is easy to apply with non-sticky saline-based wet sensors and has high research quality [16]. The data collection will be conducted by research assistants who are blinded to the participants’ group assignment. Recording will be performed in three conditions, namely, resting state, social scenes, and preferred music, for 5 min each. For the baseline resting state condition, data will be recorded with participants at rest, passively viewing an animation of moving shapes without sound. Although resting-state qEEG in adults is usually measured without explicit sensory stimulation, a simple viewing task is used here because it will be difficult for children to sit still without anything to hold their attention [16]. For the social scene condition, participants will view typical scenes where children or adults interact in school and playground without sound. For the preferred music condition, the participants will listen to their preferred music with eyes opened and fixated on a cross on a computer screen.

To determine the music preference of participants, a brief selection task of 25 different music pieces and genres will be administered, based on a task adapted from previous research reporting a five-factor music preference model called MUSIC [20]. Each music excerpt will be 15 s long, and participants will indicate their preference for each piece based on a 5-point pictorial scale. The dominant music style will be calculated for each participant and 5 min of preferred music pieces will be played to obtain neural responses to music in the pre-test and post-tests.

EEG segments free of artifacts will be selected, and spectrum decomposition will be carried out. Absolute and relative power levels in different frequency bands (alpha, beta, delta, gamma, and theta) will be calculated in each condition. FAA index will be calculated by subtracting the alpha frequency power from left and right frontal electrodes. The difference in FAA in the social scenes and baseline will be used as a predictor in data modeling in treatment and control groups. The FAA in preferred music condition will be correlated with treatment effectiveness in the treatment group only.

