Frontal alpha asymmetry (FAA) is typically investigated in relation to emotional response and motivations, both in clinical and normal populations [10]. Left-lateralized or left-dominant brain activity has been linked to an *approach* system where an individual experiences positive emotions and motivations. In contrast, right-lateralized frontal activity may reflect negative emotions and intention to withdraw. Reduced alpha power in the left frontal area of the scalp in individuals with ASD has also been reported [9]. The modulation of FAA has been demonstrated in neurofeedback training in individuals with ASD to activate their imitation behaviors [11, 12], so this measure is hypothesized to predict and be responsive to social skill interventions. High-functioning individuals with ASD show intact emotional processing when listening to music, although they demonstrate distinct neural patterns relative to neurotypical adults, which is interpreted as increased cognitive load and physiological arousal [13]. Individual preference for music varies within the target group with ASD and ID and may predict how they respond to social skill intervention using music therapy. Although self-report rating scales exist for reporting music experience and preference, qEEG measures may be superior because they index automatic responses to musical stimuli that the target population of children with ASD and ID may find difficult to understand or express.

The proposed study will address the research gap on music therapy as an intervention for social functioning in children with ASD with mild to borderline ID. The research design is to examine whether using music therapy as social skill intervention provides additional benefits relative to non-musical active control behavioral intervention in a 12-week RCT. We will also evaluate whether pre-treatment neural response to music is correlated with the effectiveness of musical social skill intervention. If correlation is found, then the long-term goal is to develop individualized intervention based on pre-treatment markers to maximize treatment efficacy.

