### Objectives

Aims and hypotheses to be tested:
On the group level, is social skill intervention using music therapy more effective in enhancing social interaction than non-musical social skill training for children with ASD and co-occurring mild/borderline ID?On the individual level, are participants with enhanced left-lateralized FAA to social scenes relative to baseline more responsive to both types of social skill interventions?For participants in the music therapy intervention, does enhanced left-lateralized FAA to preferred music relative to baseline predict better outcomes in social skill development?

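### FAA is defined as a plain difference in alpha power, so it scales with each child's overall alpha level, and the Aim 3 analysis omits the baseline contrast that the aim asks for

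*Protocol article*

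**What the plan says.** All references are to the protocol article.

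- **The index** (Secondary outcomes): "FAA index will be calculated by subtracting the alpha frequency power from left and right frontal electrodes". The text names no log, ratio or normalising step. Just before it comes "Absolute and relative power levels in different frequency bands (alpha, beta, delta, gamma, and theta) will be calculated in each condition", without saying which kind of power enters FAA.
- **Aim 2** (Objectives): "are participants with enhanced left-lateralized FAA to social scenes relative to baseline more responsive to both types of social skill interventions". The matching analysis rule (Secondary outcomes) is "The difference in FAA in the social scenes and baseline will be used as a predictor in data modeling in treatment and control groups".
- **Aim 3** (Objectives): "does enhanced left-lateralized FAA to preferred music relative to baseline predict better outcomes in social skill development". The matching analysis rule (Secondary outcomes) is "The FAA in preferred music condition will be correlated with treatment effectiveness in the treatment group only".
- **Direction** (Prediction of treatment success): "Left-lateralized or left-dominant brain activity has been linked to an" approach system, and right-lateralized frontal activity is linked to withdrawal. The one remark on the side of alpha power is "Reduced alpha power in the left frontal area of the scalp in individuals with ASD has also been reported".
- **Model** (Statistical analyses): pre-treatment frontal asymmetry, social and music, enters as a fixed effect. The control factors are IQ, age and ASD severity. Overall alpha power is not among them.

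**The concern.** FAA is the only neural predictor named for two of the three aims, and the long-term goal of individualized intervention rests on it. A predictor meant to capture lateralization should give the same value to two children with the same proportional asymmetry. A plain difference in power does not: the child with more alpha power overall gets the larger value.

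Overall alpha level is not a neutral nuisance here. The background (Prediction of treatment success) reports that alpha power is reduced in ASD and that a larger deviation from age-matched controls may go with more severe symptoms. The raw index thus mixes asymmetry with a quantity that the article itself ties to severity. If outcome depends on the asymmetry, the mixing dilutes the association that the trial is looking for, in samples of 40 per arm or fewer after attrition.

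The second problem is a mismatch between an aim and its analysis. Aim 3 asks about a change from baseline, and the analysis rule uses a level. A child whose frontal asymmetry is always strong, with or without music, would count as a strong responder to music.

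**Working it through.** The article gives no figure for FAA, so there is nothing to reproduce. The check is algebra, then a size calculation under stated assumptions.

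**1. Scaling of the raw difference.** Let left alpha power be a and right alpha power be k·a.

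- Raw difference: R − L = a(k − 1), proportional to a.
- Log difference: ln R − ln L = ln k, free of a.
- Normalised difference: (R − L)/(R + L) = (k − 1)/(k + 1), free of a.

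With k = 1.2 (illustrative levels):

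| Left alpha a | R − L | ln R − ln L | (R − L)/(R + L) |
|---|---|---|---|
| 2 | 0.4 | 0.182 | 0.091 |
| 10 | 2.0 | 0.182 | 0.091 |
| 40 | 8.0 | 0.182 | 0.091 |

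**2. Do other parts of the plan remove this?**

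- *Subtracting baseline (Aim 2).* Let the sides be equal at baseline and the right side 10% higher in the condition. The raw change is 0.1a = 0.2, 1.0 and 4.0 at the three levels. The log change is ln 1.1 = 0.095 at each.
- *Relative power.* At left alpha shares of 10%, 20% and 40% with k = 1.2, the difference is 0.02, 0.04 and 0.08. Dependence on total signal amplitude falls, but dependence on alpha share stays.
- *Age and severity as covariates.* These enter additively. They shift the expected outcome and do not undo a multiplicative factor inside the predictor.

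**3. Size of the loss.** Assumptions, none of them from the document:

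- overall alpha A is log-normal with log-SD s;
- A is independent of the log-ratio asymmetry x;
- x is small and centred at zero;
- outcome depends on x.

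With L = A·exp(−x/2) and R = A·exp(x/2), R − L ≈ A·x. Then

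corr(Ax, x) = E[A]/√E[A²] = exp(s²/2)/exp(s²) = exp(−s²/2).

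| s | exp(−s²/2) |
|---|---|
| 0.4 | 0.92 |
| 0.6 | 0.84 |
| 0.8 | 0.73 |
| 1.0 | 0.61 |

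The same factor applies to a condition-minus-baseline change. A simulation of that change score (400,000 draws, SD of the log-ratio 0.15 at baseline and for the change) gave 0.96, 0.88, 0.73 and 0.60 at s = 0.3, 0.5, 0.8 and 1.0. A true predictor–outcome correlation of 0.30 then appeared as 0.29, 0.27, 0.22 and 0.18.

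**4. What that means with 40 music-arm children.** Take an assumed true correlation of 0.45. By the Fisher approximation, two-sided α = 0.05, power = Φ(atanh(r)·√37 − 1.96).

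- No dilution, r = 0.45: 0.485 × 6.08 − 1.96 = 0.99, power about 84%.
- s = 0.6, r = 0.45 × 0.84 = 0.38: power about 68%.
- s = 0.8, r = 0.45 × 0.73 = 0.33: power about 55%.

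**5. Aim 3 against its analysis rule.** Let M be music-condition FAA and B baseline FAA, with equal variance and correlation ρ (both assumptions). Then corr(M, M − B) = √((1 − ρ)/2), which is 0.71, 0.50 and 0.32 for ρ = 0, 0.5 and 0.8. The level and the change are different predictors, and they diverge further the more stable a child's asymmetry is.

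**6. Order of subtraction.** L − R is the exact negative of R − L. In the simulation at s = 0.5 the correlation was +0.27 one way and −0.27 the other. The two-sided p-value is the same.

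**The case against.** **The sentence is a summary.** A journal article condenses, and a log transform, electrode pair and sign convention could all stand in a fuller protocol or analysis plan that is not shown. This stands in part: absent electrode names or an absent order of subtraction would not be a finding alone. But the article does state how the index is formed, and the operation stated is a subtraction of power. Followed as written, it gives the scaling shown above.

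**The size is assumed.** This stands. The spreads, the independence of level and asymmetry, and the premise that outcome follows proportional rather than absolute asymmetry all come from outside the document. At small spreads the loss is minor.

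**The log difference is one choice among several.** Also true. The normalised difference removes the scaling equally well.

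**The music rule may be shorthand.** The model description lists social and music asymmetry together, so a baseline contrast may be intended for both. But Secondary outcomes spells out the difference for social scenes and, in the next sentence, does not for music.

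**A stronger reading is tempting.** A reader might infer that, with no order of subtraction and no stated link from alpha power to activity, the directional aims could be claimed as supported whichever way the data fall. The documents do not support that. The background ties left-lateralized to left-dominant activity and approach, the aims use the same word, and the CARS-2 and SRS-2 sections say that high scores mean greater impairment. The intended direction is readable. What is missing is a convention linking the sign of the index to that direction, and this leaves the two-sided p-value unchanged.

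**Conclusion.** The point holds in two parts.

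First, the stated index is not scale-free. The algebra is exact and needs no assumption: the same proportional asymmetry gives values that differ in proportion to overall alpha. Neither relative power, baseline subtraction nor the listed covariates remove this. The resulting loss of correlation ranges from 8% (s = 0.4) to 39% (s = 1.0) under the assumptions in the working, so it may be small or material, and the document cannot settle which.

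Second, the Aim 3 analysis rule does not match Aim 3. This rests on the text alone.

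The unstated order of subtraction is a clarification to make in passing, not a fault that leaves the aims open to either reading. It would also be wrong to infer a threat to the trial's main result: the comparison of interventions on CARS-2 and SRS-2 (Aim 1) does not depend on how FAA is scaled. The change is worth making because it is nearly free and bears on two of the three aims.

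**What to change.** Before outcome data are analysed, replace the FAA sentence in Secondary outcomes with a definition that does four things:

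1. Makes the index scale-free, for example ln(right frontal alpha power) minus ln(left frontal alpha power). The normalised difference (R − L)/(R + L) is an acceptable alternative.
2. Uses the condition-minus-baseline difference of that index for both Aim 2 (social scenes) and Aim 3 (preferred music), so that the Aim 3 analysis matches its objective.
3. States the order of subtraction and which sign is read as left-lateralized. The sponsor needs to supply the link from alpha power to activity, which the article leaves out.
4. States the expected sign of the coefficient, given that higher CARS-2 and SRS-2 scores mean worse impairment.

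The cost is a short rewording and one line of analysis code. The resting-state recording needed for the baseline contrast is already planned, so no new data are required. The one drawback is that results are no longer in raw power units. If the sponsor wants those, the raw difference can be reported as a sensitivity analysis.
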